#### Secondary outcome analysis

We believe the two key secondary outcomes (cancer worry, breast cancer self-efficacy) will provide supportive information about the effectiveness of the iCanDecide-ESE and Clinician Dashboard on the primary outcome of knowledge. A gatekeeping statistical strategy will be used to control the type I error rate at 0.05 across the primary and this key secondary family of outcomes such that when both effects on the primary outcome of knowledge are demonstrated, this family of key secondary outcomes will be examined and may contribute important supportive information about the effectiveness of the interventions. The secondary family of tests comprises four tests (two for each secondary outcome) that will be conducted and will be tested with the Holm procedure [29]. The linear mixed model described will be separately fit for each continuous outcome (cancer worry; self-efficacy). The self-efficacy (or cancer worry) effect of the individual-level intervention will be quantified by the coefficient 𝜃_1_. The estimate of the effect of the Clinician Dashboard cluster-level intervention on self-efficacy (or cancer worry) will be quantified by the coefficient 𝜃_2_.

### Interim analysis {21b}

There is no planned interim analyses.

### Additional analyses {20b}

Additional secondary outcomes (HCCQ, PACE, SDQ) will be explored following the primary analysis described above. Concordance is a binary outcome reflecting whether the treatment received was concordant or not with the patient’s emotional support measures so a logistic random effects model similar to that above will be used.

The clinician measures that are collected at three time points (upon registration, 9 and 18 months after registration) will be compared. The purpose is to assess whether scores in clinician reported ability to deliver PCC (using the two measures included in their survey) increase as their clinic is exposed to using the Clinician Dashboard. There is no formal statistical testing planned for analysis of these measures.

### Methods to handle protocol non-adherence and statistical methods to handle missing data {20c}

This is an intent-to-treat analysis. We will measure our primary and key secondary outcomes by patient report in the first follow-up survey, 5 weeks post-surgery. We anticipate we will have minimal missingness at this time point based on our prior iCanDecide trial [3] for which we obtained 92% complete follow-up survey data at the same measurement time point. However, to decrease missing data from follow-up survey, assessment burden, and dropout, we have limited the number of survey questions and provided incentives. We have included flexible means of contacting patients, including email (primary modality), telephone, or regular mail. If data are missing on predictor variables of interest, data will be imputed using multiple imputation (MI) techniques (MI using chained equations) [34]. MI produces valid statistical estimates under missingness at random (MAR), while also accounting for additional uncertainty arising from missing data. We will perform sensitivity analyses to determine the degree to which results are sensitive to the MAR assumption. We will also account for survey non-response using an inverse probability weighting approach if we should find that there is differential survey non-response between the intervention and usual care groups according to patient characteristics that also influence the outcomes of interest. We will consider patients as participants if they complete enrollment and the baseline tailoring survey and only consider them to have dropped out if they withdraw consent. If a participant withdraws consent, we will document (1) the reason for dropout, (2) who decided the participant would drop out, and (3) whether the dropout involves some or all types of participation.

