**Methods/design:**

This study will implement a multilevel intervention with patient and clinician components as a NCORP Cancer Care Delivery Research (CCDR) trial within the Alliance for Clinical Trials in Oncology Research Base (Alliance). The two interventions in this study, the *Shar*ed Decision *E*ngagement *S*ystem (SharES), include (1) two versions of an evidence-based patient-facing breast cancer treatment decision tool (iCanDecide +/− an emotional support module) and (2) a clinician-facing dashboard (Clinician Dashboard) that is reviewed by surgeons/clinicians and summarizes ongoing patient needs. The design is a near minimax, hybrid stepped wedge trial of SharES where both interventions are being evaluated in a crossed design over six 12-week time periods. The primary outcome (knowledge) and key secondary outcomes (i.e., self-efficacy and cancer worry) are assessed via patient report at 5 weeks after surgery. Secondary outcomes are also assessed at 5 weeks after surgery, as well as in a second survey 9 months after registration. We anticipate recruiting a total of 700 breast cancer patients (600 evaluable after attrition) from 25 surgical practices affiliated with Alliance.

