#### Patients need help to manage the complexity of information

Although having an accurate understanding about treatment trade-offs is a key component of an informed decision, patients’ knowledge is surprisingly low. In part, this is due to the complex and often overwhelming nature of the clinical information and treatment decisions a patient must make. Several breast cancer decision tools aimed exclusively at the patient have been developed and tested. In general, these patient-facing tools have been modestly successful at improving knowledge about treatment options. Indeed, our patient-facing decision tool (“iCanDecide”) was effective in improving knowledge about complex treatment tradeoffs using an innovative “knowledge building” approach. We systematically built knowledge by first educating patients with very simple information about key facts related to their treatment; we found that 60% of patients in the intervention arm had high knowledge (defined as at least 80% of knowledge items correct) 4 weeks after enrollment and treatment, compared with 42% who viewed a static version without knowledge building (*P* < 0.001) [3]. Importantly, knowledge deficits are especially concerning in more vulnerable groups, such as those with lower educational attainment and racial/ethnic minorities (particularly those who are non-native English speakers) [4, 5]. We believe this knowledge building approach should be the standard of care for educating patients, and particularly for those most vulnerable to low knowledge where gains are most needed. However, with patient input, we identified two additional strategies that merit inclusion in patient decision support tools: (1) supporting the emotional aspects of diagnosis and (2) more directly engaging clinicians in the process of supporting shared decision-making.

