### Sample size {14}

Sample size depends on the near minimax stepped wedge/parallel hybrid design as described by Girling and Hemming [28]. This design provides close to the maximal possible efficiency across a range of intra-cluster correlations (ICCs) from 0 to 0.2, where larger ICCs are expected for our primary outcome of knowledge as seen from the prior iCanDecide randomized clinical trial (RCT) [3]. Specifically, in our previous iCanDecide trial, we calculated an ICC of 0.15 and a moderate effect size for the iCanDecide decision tool of 0.5 standard deviations. This effect size is equivalent to a little less than one additional question being answered correctly by those who received the intervention.

For SharES, we calculated the sample size required to detect a somewhat smaller standardized effect size of 0.35, which results in only two out of three women getting an additional question correct. Thus, for the planned hybrid stepped wedge design testing the clinic level intervention, we will recruit 25 clinics with a target total sample size of 600 evaluable patients (approximately four patients per clinic per time period) [28–31]. We estimate about 15% will not complete the first follow-up assessment (5 weeks post-surgery), based on our prior iCanDecide trial [3], so we plan to enroll at least 700 participants or around 5 patients per clinic per period. This will allow us to have at least 80% power (alpha=0.05) to detect differences of 0.35 standard deviations between intervention and control subjects for the clinic level intervention (Clinician Dashboard vs. none) and 0.25 standard deviations for the individual-level intervention (ICanDecide-ESE vs. ICanDecide-S) across a wide range of ICCs (0.01 to 0.20). The interaction effect between the two interventions would have to be at least 0.5 standard deviations, or about one additional question correct for each subject, comparable to our effect size in our current intervention, for us to be able to detect it at conventional significance levels.

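### The prior trial is credited with two different completion rates, and the stated missing-data rule imputes predictors while the knowledge score that non-completion removes gets only a conditional correction

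*Protocol article*

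**What the plan says.** Sample size {14} of the protocol article sets a "target total sample size of 600 evaluable patients (approximately four patients per clinic per time period"). It then says: "We estimate about 15% will not complete the first follow-up assessment (5 weeks post-surgery), based on our prior iCanDecide trial", and continues "so we plan to enroll at least 700 participants or around 5 patients per clinic per period". The abstract agrees: "We anticipate recruiting a total of 700 breast cancer patients (600 evaluable after attrition) from 25 surgical practices".

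The section on non-adherence and missing data {20c} expects little missing data at the same assessment, because of the prior iCanDecide trial "for which we obtained 92% complete follow-up survey data at the same measurement time point". For the handling of gaps it states: "If data are missing on predictor variables of interest, data will be imputed using multiple imputation (MI) techniques". It adds sensitivity analyses to the missing-at-random (MAR) assumption. Inverse probability weighting (IPW) for survey non-response is to be used if that non-response is found to differ between the intervention and usual care groups by patient characteristics that also affect outcome.

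The primary outcome analysis is a linear mixed model with patient arm, dashboard status, period and a random clinic intercept. Race and education, the two factors balanced in the patient-level allocation, enter only in a supportive analysis, together with a Hispanic/Latina indicator.

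**The concern.** Two points need attention.

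First, 15% non-completion and 92% completion cannot both be the prior trial's experience of the same assessment. A reader cannot tell whether 15% is an observed rate or a cautious planning value, nor whether the expectation of little missing data is justified.

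Second, the imputation rule is aimed at the wrong variables for the primary model. Arm, dashboard status, period and clinic are known for every enrolled patient. Non-completion of the follow-up survey removes the knowledge score. Each patient contributes a single score at a single time, so the mixed model has no other outcome value from that patient to draw on, and the primary fit is a complete-case fit. It is unbiased when non-response depends only on terms in the model. Race and education are not among those terms, although the patient-level randomization section calls them prognostic for knowledge in particular. Whether anything corrects for them depends on a look at the data with no stated criterion. At stake is a primary estimate whose method is partly chosen after the non-response pattern is seen.

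**Working it through.** 1. **The plan's own enrolment figure** (Sample size {14}). Evaluable target: 25 clinics × 6 periods × 4 = 600. Enrolment at 15% loss: 600 / (1 − 0.15) = 705.9. The stated figure is at least 700. In reverse, 600 / 700 = 0.857, a loss of 14.3%, which fits about 15%. The figure is reproduced up to rounding.

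2. **The two loss rates side by side**, per 700 enrolled.
   - 15% (Sample size {14}): 700 × 0.15 = 105 missing, 700 × 0.85 = 595 evaluable.
   - 8% (section {20c}, 1 − 0.92): 700 × 0.08 = 56 missing, 700 × 0.92 = 644 evaluable.
   - Ratio of missing outcomes: 105 / 56 = 1.9.

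3. **Dashboard power** at 0.35 SD. Inputs from the article: 5 clinics always on, 5 never on, 3 starting at each of T2 to T6, six periods, ICC 0.01 to 0.20. Assumed: two-sided alpha 0.05, equal clinic-period sizes m = N / 150, total variance 1, random clinic intercept only, the dashboard test taken on its own. The clinic's period means have covariance V = ICC·J + ((1 − ICC)/m)·I, where J is the 6 × 6 matrix of ones and I the identity. The SE of the dashboard effect comes from inverting the sum over clinics of D′V⁻¹D, where D holds the period and dashboard indicators. Power = Φ(0.35/SE − 1.96).
   - N = 595: 95.6% at ICC 0.01, 83.3% at ICC 0.20.
   - N = 600: 95.7% and 83.5%.
   - N = 644: 96.7% and 85.6%.

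4. **Patient-level power** at 0.25 SD, ignoring the clinic effect: Φ(0.25/√(4/N) − 1.96).
   - N = 595: Φ(3.049 − 1.96) = 86.2%.
   - N = 600: Φ(3.062 − 1.96) = 86.5%.
   - N = 644: Φ(3.172 − 1.96) = 88.7%.

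5. **What imputation of predictors can reach.** In the primary model: arm (assigned), dashboard status (set by clinic and period), period, clinic. None can be missing. Race and education are used by the dynamic allocation, so they should be known at randomization too.

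6. **What triggers weighting.** The trigger is a difference between intervention and usual care. In the iCanDecide-ESE versus iCanDecide-S contrast every patient receives a version of the tool, so no usual care group exists there. The wording fits only the dashboard contrast, and no threshold or test is given for either.

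7. **Illustrative bias** in the patient-level contrast (assumed inputs, not from the article). Response is 85% except for lower-education patients in one arm, where it is 75%. The lower-education share is p and the knowledge gap by education is 0.5 to 1 SD. The share among responders in that arm is 0.75p / (0.75p + 0.85(1 − p)).
   - p = 0.2: 0.15 / 0.83 = 0.181, shift 0.019, bias 0.010 to 0.019 SD.
   - p = 0.4: 0.30 / 0.81 = 0.370, shift 0.030, bias 0.015 to 0.030 SD.
   - Against the 0.25 SD design effect, this range is 4% to 12%.

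**The case against.** **The sample size uses the larger loss, so nothing is harmed.** This stands for power: steps 3 and 4 stay above 80% throughout. It is also possible that 15% was meant as a margin, or that the 92% measures something else, such as item completeness. The Background places the prior knowledge outcome "4 weeks after enrollment and treatment", so even the claim of an identical time point needs tightening. But the article presents 15% as based on the prior trial, not as a margin over it, and one sentence would settle the matter.

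**A reader might infer that the enrolment target is miscalculated**, since 700 × 0.85 = 595 and five per clinic-period would be 25 × 6 × 5 = 750. The article does not support that. Its figures are explicitly approximate, 700 / 150 = 4.67 rounds to five, and the shortfall of five patients moves power by about 0.3 points at most.

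**A reader might infer that the 92% figure is the reason for imputing predictors only.** The text makes no such link. The figure supports only the expectation of little missing data, and imputation is introduced separately.

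**A reader might infer that missing outcomes are ignored.** They are not: IPW and MAR sensitivity analyses are both named. An available-case mixed model with these in support is a recognised approach. What remains is that the weighting is conditional on an undefined finding, and that sensitivity analyses probe the primary estimate without changing it. Since no test is named, how often the check would miss a real difference cannot be judged.

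**Predictors outside the primary model may be missing**, for example the Hispanic/Latina indicator in the supportive analysis. This is fair, so imputation of predictors has some use. It does not help the primary analysis.

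**Conclusion.** The concern holds as a contradiction to reconcile and as a missing-data rule that is poorly aimed. The contradiction is 15% against 8% loss, 105 against 56 missing outcomes per 700, from one cited source. It does not threaten the stated power, on the assumptions of two-sided testing and equal clinic-period sizes. In the missing-data rule, imputation is stated for variables that the primary model always has, while the knowledge score depends on a complete-case fit and a correction with no stated criterion and a comparator that does not exist in the patient-level contrast. The practical bias is likely small, 0.01 to 0.03 SD in a scenario whose inputs are assumed. A claim of large bias, or of an underpowered or miscalculated trial, would go beyond the article. The case for change is that the rules are stated now, can be made firm cheaply, and should not depend on the observed non-response.

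**What to change.** - Give one non-completion figure in Sample size {14} and section {20c}, or state that 15% is a deliberate margin over the 8% seen in the prior trial. The enrolment target need not change.
- Include race and education in the primary mixed model for knowledge, instead of only in the supportive analysis. This covers non-response related to those factors and can gain precision.
- Pre-specify one method for missing knowledge scores and carry it out whatever the observed non-response. One choice is multiple imputation of the score from arm, dashboard status, period, clinic, race, education and the knowledge answers given inside the tool. The in-tool answers come after randomization, so they belong in the imputation model and not as covariates in the analysis model. The other choice is IPW, defined separately for each of the two contrasts.
- Keep the planned MAR sensitivity analyses, and keep imputation of predictors for the supportive models that need it.

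The cost is corrected text and modest programming. Every variable is already collected, and neither the design nor the sample size changes.

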### Plans to give access to the full protocol, participant-level data, and statistical code {31c}

The full protocol resides with the NCI Central IRB and is available as a supplement. In accordance with the Alliance, data may be available upon request to the Principal Investigator.

## Oversight and monitoring

### Composition of the coordinating center {5d}

The study team includes the Principal Investigators and staff based at the coordinating center (University of Michigan) and those from the Alliance for Clinical Trials in Oncology cooperative group. The Alliance is led by a Group Chair who answers to a Board of Directors made up of clinical site principal site investigators from 50 Alliance member institutions. The vision for the Alliance is to reduce the impact of cancer by uniting a broad community of scientists and clinicians who are committed to the prevention and treatment of cancer.

### Composition of the data monitoring committee {21a}

The Alliance Data and Safety and Monitoring Board meets every 6 months (or more, if needed) and reviews the study progress. It is chaired by independent members. A report is submitted to the study Principal Investigators and team following each meeting.

### Adverse event reporting and harms {22}

This is a very low risk study of an educational intervention for patients and clinicians. Prior such studies have not generated any adverse events. However, should a participant feels distressed as a result of study participation, we encourage them to contact the Alliance study team as listed in the informed consent.

### Frequency and plans for auditing trial conduct {23}

The Alliance will monitor all aspects of the study on an ongoing basis.

### Plans for communicating important protocol amendments to relevant parties {25}

Changes to the protocol will follow the Alliance process for submission to the NCI Central IRB. Once approved, the existing protocol is updated, and participating clinics are made aware of updates via regular all-site meetings.

### Dissemination plans {31a}

The team will develop plans for publication and dissemination of results. This will follow the publications requirements of the Alliance Publications Committee. We will share all results with participating clinics, as well as with the Alliance CCDR Committee. We will work with the Alliance and participating sites to ensure patient participants are aware of publications resulting from this study.

## Discussion

Breast cancer patients face a challenging landscape of decisions that start at the time of diagnosis. A cancer diagnosis often triggers additional worry and distress that make it difficult for patients to make high quality decisions about their care. While decision support tools focused on the cognitive aspects of decision making exist, specifically helping to improve patients’ understanding of their disease and treatment options, there are none that also help to manage the emotional aspects of a cancer diagnosis. Doing so may help patient better accept and understand more cognitive information. Furthermore, while decision tools are often intended to support patient-provider communication and shared decision making, few existing tools “close the loop” by helping providers understand where patients may have deficits to decision making. Our study, an RCT of a Shared Decision Engagement System, specifically focuses on addressing both gaps in decision making intervention research by (1) helping support the emotional aspects of decision making by offering patients tools to manage worry and distress and support coping and (2) providing their surgeons with a dashboard that will help them review where the patient is with regard to her decision process and address any lingering deficits. Through this multilevel intervention trial, we aim to improve PCC in order to improve outcomes for newly diagnosed breast cancer patients.

## Trial status

Protocol version: 1

Date when recruitment was initiated: 1 March 2021

Date when recruitment will be completed (approximate): 1 September 2023

## Data Availability

Any data required to support the protocol can be supplied upon request.

## Abbreviations

CCDR: Cancer Care Delivery
CHCR: Center for Health Communications Research
CRA: Clinical Research Assistant
HCCQ: Healthcare Climate Questionnaire
NCI: National Cancer Institute
NCORP: NCI Oncology Research Program
PACE: Patient Assessment of Cancer Experiences
PCC: Patient-centered communication
RCT: Randomized controlled trial
SDC: Statistics and Data Center
SDQ: Subjective Decision Quality
SharES: Shared Decision Engagement System
